### Endpoints

#### Primary Endpoints

The first endpoint will be the condition suggestion accuracy and comprehensiveness of the prototype DDSS, evaluated against the gold standard differential diagnosis determined by the review panel, reported in the context of the accuracy of the usual HCP. The second endpoint will be the study HCP’s condition suggestion accuracy and comprehensiveness, which will be compared between arm 1 (in which the HCPs determine their own list of condition suggestions before seeing the prototype DDSS’s condition suggestions, then create a final ranked list of condition suggestions) and arm 2 (in which they see the prototype DDSS’s condition suggestions before determining their list of overall ranked condition suggestions). The third endpoint will be a comparison of the study HCP's condition suggestion accuracy and comprehensiveness in arm 1 in the preliminary and final DDLs.

#### Additional Data of Interest

Additional data of interest will include qualitative data on the usability, usefulness, and acceptability of the prototype DDSS.

### Outcomes and Outcome Measures

The design of this study is based on the literature on pilot study design, as it will serve as a guide for a larger trial in the future [36,37]. The sample size of a minimum of 50 participants was a pragmatic determination of a number of participants that could be used to assess the ability to recruit patients across a spectrum of conditions in a clinic of this type and in this setting, to evaluate the feasibility of collection of the complete study data, and to allow an accurate analysis. There are multiple aspects of study design and operation that will be explored in this pilot study: (1) investigating if it is feasible to determine the accuracy and comprehensiveness of the Ada DDSS for a large range of symptoms and conditions in multiple different age groups; (2) establishing how many patients and HCPs can be recruited and the likely number of completed patient and HCP questionnaires; (3) trialing new methods and enabling power calculations intended to be used in a later single- or multicenter randomized controlled trial; and (4) evaluating the general feasibility, both technical and logistical, of a full-scale study, including issues of data collection and questionnaire design. The pilot has not been powered to definitively accept or reject the scientific hypotheses, as a pilot is required before the sample size for a definitive study can be estimated.

### Risk-Benefit Assessment

This study does not pose any risk to the patients, as it is solely observational; therefore, there is no need for additional safety management. Patients requiring immediate medical care and clinically unstable patients will be excluded. If patients are called into their appointment before the study HCP finishes the prototype DDSS assessment, they will be excluded from the study process and analysis and proceed to usual care, meaning there will be no delay in the diagnosis or treatment of any patient. Although there will be 2 extra consultations for patients enrolled in the study, these consultations will generally require less than 10 minutes; therefore, it is highly unlikely to delay a patient’s diagnosis or treatment.

### Data Management and Data Safety

This study has a data management plan that outlines the guidelines by which data entry will take place. All consent forms will be paper based; the rest of the data will be collected electronically. Paper records will be kept in a locked cabinet in the facility only accessible by study-specific personnel, while for electronic data, a clinical-trial electronic data capture (EDC) system (REDCap) will be used. Overall, study-site data collection will go through a secured local area network, allowing data sharing on site. Study personnel, who will be provided unique usernames and passwords, will be trained on the EDC system. Before committing data to the EDC system, the research assistant will first verify that the data are correct. After this, the research assistant will not have access to the data, as they will be automatically locked after each commit. Storage of the data will last a minimum of 3 years from the date that the last patient is seen at Muhimbili University of Health and Allied Sciences; 10% of the digitized usual care consultation notes will undergo source-data verification.

### Data Analysis

Applying the definition from Gilbert et al [31], we will assess the accuracy and comprehensiveness of the top-1, top-3, and top-5 suggested conditions by the prototype DDSS in comparison to the gold standard differential diagnoses. Data analysis will also be carried out as presented by Gilbert. In short, descriptive tests and statistics appropriate for categorical data will be utilized to compare condition suggestion accuracy. To analyze if the proportion of correct condition suggestions from the prototype DDSS, from the usual HCPs, and from the study-provided physicians are drawn from the same distributions, the chi-squared test will be applied. If there is a significant difference, we will apply a 2-sided post hoc pairwise Fisher exact test to compare the prototype DDSS and the practitioners. Due to the low sample size of this pilot study, it may be the case that the chi-squared tests will not produce significant results. As the study goal is the comparison of the prototype DDSS to usual care, the ratings of the usual HCPs will be strictly anonymized.

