### Objective and Hypotheses

This study is part 2 of the AFYA (Artificial Intelligence-Based Assessment of Health Symptoms in Tanzania) study series [20]. The current study will explore the potential of the prototype DDSS to empower HCPs in LMICs. The objective is to measure to what degree the prototype DDSS can enhance the diagnostic accuracy of mid-level HCPs. This will be done by comparing, in an observational study setting, the diagnostic accuracy of HCPs who use the study tool to HCPs performing usual care, henceforth referred to as usual HCP, and by comparing the accuracy of diagnoses submitted before and after input from the DDSS. Since impracticality is a common barrier to CDSS adoption [8,9], we will also collect qualitative data on the usability, usefulness, and acceptance of the prototype DDSS. These measurements will provide insights on the appropriateness of the prototype DDSS interface.

There are two study hypotheses: (1) a “chatbot”-based DDSS, which is similar to a symptom assessment app (SAA) as it asks a series of questions about the patient’s symptoms using a sequential “question flow,” is an appropriate interface for improving the accuracy of decision-making by mid-level HCPs in sub-Saharan Africa; and (2) the diagnostic accuracy of mid-level HCPs will be improved by the use of a “question flow” DDSS based on a chatbot.

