The matching of conditions by the physician panel in step 5 will involve matching the diagnoses made by the usual HCP and study-provided physician with the diagnoses made by the reviewer physicians on the physician panel. The same procedure for the DDSS condition list will be carried out by the reviewer physicians. As in step 4, a third reviewer physician will make a final decision if there is disagreement between the 2 reviewer physicians. The primary comparator of the Ada assessment is the differential diagnosis obtained before the addition of vital sign measurement, physical examination, and additional diagnostic tests. Looking at the differential diagnosis list at each point in the patient’s clinical journey is still a relevant point of comparison.

Finally, the data collection performed in these 5 steps will be analyzed (details are in the “Data Analysis” section). In order to determine the usability, usefulness, and acceptability of the prototype DDSS, the usual HCP questionnaires, in addition to the patient questionnaires, will be analyzed and described using methods appropriate to modified Likert-scale questionnaire data [26].

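### The first comparison named in the objective (HCPs using the tool versus usual HCPs) has no primary endpoint, and endpoints 2 and 3 answer narrower questions

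*Protocol article*

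**What the plan says.** All references are to the Protocol article.

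- **Objective and Hypotheses.** "The objective is to measure to what degree the prototype DDSS can enhance the diagnostic accuracy of mid-level HCPs". Two routes are given. Route A compares "the diagnostic accuracy of HCPs who use the study tool to HCPs performing usual care". Route B works "by comparing the accuracy of diagnoses submitted before and after input from the DDSS". Hypothesis 2 is that a question-flow, chatbot-based DDSS improves the accuracy of mid-level HCPs.
- **Primary Endpoints.** Endpoint 1 is the accuracy and comprehensiveness of the DDSS itself against the panel's gold standard, set beside usual-HCP accuracy. Endpoint 2 is the study HCP's accuracy in arm 1 against arm 2; the arm 1 description has HCPs make their own list and "then create a final ranked list of condition suggestions". Endpoint 3 is arm 1 only, preliminary against final list.
- **Ada Assessment by Study HCP (Stage 1).** The study HCP assesses the patient with the DDSS in both arms. The arm 1 preliminary list is locked before the suggestions appear, and the arm 1 final list is then chosen from the HCP's own list and the tool's. The arm 2 list is made after the suggestions are seen.
- **Data Analysis.** A chi-squared test asks whether proportions correct "from the prototype DDSS, from the usual HCPs, and from the study-provided physicians are drawn from the same distributions", followed by pairwise Fisher tests of the DDSS against the practitioners. A later sentence begins "As the study goal is the comparison of the prototype DDSS to usual care".

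**The concern.** Hypothesis 2 is about a clinician who has the tool. The endpoint that refers to usual care, and the tests that are spelled out, are about the software without the clinician. How accurate the software's list is and how accurate an HCP becomes when using it are different quantities: an HCP may ignore a correct suggestion or adopt a wrong one.

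If the endpoints are followed as written, Route A is never reported, although both lists it needs are collected. The two endpoints that do involve the study HCP would then carry the whole weight of hypothesis 2, and endpoint 2 in particular invites misreading. The pilot is also meant to enable power calculations for a later randomized trial (Outcomes and Outcome Measures), and those need an estimate of the contrast that such a trial would be about.

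**Working it through.** **1. Mapping the objective to endpoints and named tests**

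| Comparison | Primary endpoint | Named test |
|---|---|---|
| Route A: study HCP with tool vs usual HCP | none | none |
| Route B: before vs after DDSS input | endpoint 3 | none |
| Software's list, in the context of usual HCPs | endpoint 1 | chi-squared, then Fisher |
| Study HCP, arm 1 vs arm 2 | endpoint 2 | none |

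**2. What each contrast estimates**

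Additive notation, for exposition only. Let *a* be the study HCP's accuracy without the tool, *q* the gain from the question flow, *s1* the gain from the suggestions when seen after committing to a list (arm 1), *s2* the gain when seen first (arm 2), and *u* the usual HCP's accuracy.

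- Arm 1 preliminary = *a + q*
- Arm 1 final = *a + q + s1*
- Arm 2 final = *a + q + s2*

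Then:

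- Endpoint 3 = (*a + q + s1*) − (*a + q*) = *s1*.
- Endpoint 2, final vs final = (*a + q + s1*) − (*a + q + s2*) = *s1 − s2*, an order or anchoring effect.
- Endpoint 2, if the arm 1 preliminary list was meant: arm 2 minus arm 1 = *s2*.
- Route A, arms pooled equally = *q* + (*s1 + s2*)/2 + (*a − u*).

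The question-flow gain *q* cancels from endpoints 2 and 3 on either reading. Yet the section on the DDSS specifications and rationale places part of the expected benefit in the question-flow prompting, and hypothesis 2 is framed around it. Of these contrasts only Route A contains *q*. It also contains *a − u*, the difference between two sets of clinicians.

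The final-vs-final result *s1 − s2* can be zero with *s1* and *s2* both large, or non-zero with both small. It need not track the benefit of the tool.

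**3. Size**

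The minimum of 50 is called pragmatic, with no alpha, power or effect size, so there is no figure to reproduce. Alternate allocation gives about 25 per arm.

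- *Endpoint 2, unpaired, 70% accuracy assumed in both arms:* half-width = 1.96 × √(2 × 0.7 × 0.3 / 25) = 1.96 × 0.1296 = 0.254, about 25 points. At an assumed 50% it is 27.7 points, and at 82.4% it is 21.1.
- *Route A, paired on 50 patients, 70% vs 50% assumed, within-patient correlation φ assumed:* variance = [0.21 + 0.25 − 2φ√(0.21 × 0.25)] / 50, where √0.0525 = 0.2291.
  - φ = 0.19: (0.46 − 0.0871)/50 = 0.00746; SE 0.0864; half-width 0.169.
  - φ = 0.48: (0.46 − 0.2200)/50 = 0.00480; SE 0.0693; half-width 0.136.

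  That is about 14 to 17 points. The documents give neither the accuracies nor φ.
- *Power, for scale:* take the background study's 74.1% without and 82.4% with a DDSS as proportions, at an assumed two-sided 0.05. With 25 per arm, pooled SE = √(2 × 0.7825 × 0.2175 / 25) = 0.1167 and unpooled SE = 0.1161, so power = Φ[(0.083 − 1.96 × 0.1167)/0.1161] = Φ(−1.26), about 10%. Estimates with intervals are therefore the useful output.

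**The case against.** **Points that stand**

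- A reader might infer that the whole objective lacks an endpoint. It does not: Route B is endpoint 3, with the same HCP and the same patient, and that is a sound estimate of what the suggestion list adds.
- A reader might infer that the study HCP's lists are never matched to the gold standard, because step 5 in Measurement Methods speaks of "matching the diagnoses made by the usual HCP and study-provided physician with the diagnoses made by the reviewer physicians on the physician panel" and then of the DDSS list only. Stage 1 says the panel will judge the study HCP's lists in a later step, so matching is planned and the step 5 description is simply less complete.
- A reader might infer that endpoint 2 is expected to be about zero. That does not follow. An order effect can be real, committing before or after seeing suggestions is a deliberate workflow contrast, and the article nowhere offers endpoint 2 as the test of benefit.
- Missing test names would be a weak complaint alone. Data Analysis is a summary, it has a general sentence on categorical statistics, and an analysis plan that is not shown may name more.
- Route A is confounded. Usual HCPs may be COs, AMOs or medical doctors (Stage 2), whereas study HCPs are COs or AMOs and outside the patient's care. Pairing by patient does not remove this, which argues against making Route A the lead comparison.

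**Points that stand only in part**

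- The goal sentence in Data Analysis mainly explains why usual-HCP ratings are anonymized and may be shorthand. It still names a different comparison from the objective, in the section that fixes the tests.
- The pilot is expressly not powered for its hypotheses. That excuses wide intervals, not an objective whose first-named comparison is absent from the primary endpoints.

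**Conclusion.** The concern holds in a limited form. Within this one document, the first of the two comparisons that define the objective has no primary endpoint, and the analysis section describes the goal as software against usual care. Endpoint 3 covers the second comparison but only for the suggestion list. Endpoint 2, on the natural final-vs-final reading, answers an order question, and a null there should not be read as no benefit. The article does not say outright which arm 1 list is meant; on the other reading endpoint 2 still omits the question flow.

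This should be corrected, but it does not undermine the study: the lists are collected and sent to the panel, and the pilot claims no definitive test. The mismatch rests on the text alone. The half-widths (about 25 points for endpoint 2, about 14 to 17 for the paired contrast) rest on the assumed accuracies and correlations and serve only to show scale.

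**What to change.** 1. Add an endpoint: the study HCP's final list against the usual HCP's list on the same patient, as a paired difference in accuracy with a 95% CI, both arms pooled. Report it by usual-HCP cadre (CO or AMO versus medical doctor), and state that different clinicians are compared, so tool and clinician are not fully separable.
2. In endpoint 2, state which arm 1 list is used. If it is the final list, label the contrast as an order or anchoring question and say that a null is not evidence of no benefit.
3. Keep endpoint 3 as the within-HCP estimate of the suggestion list's added value, and note that its preliminary list already follows the question flow.
4. Reword the goal sentence in Data Analysis to agree with Objective and Hypotheses.

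The cost is endpoint and analysis wording; no new data are needed. The downside is one more comparison in an unpowered pilot, partly confounded by clinician. The change is best dated before the panel's matching results are available.

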### Measurement Methods

Overall, there will be 5 stages in the process of data collection and physician panel assessment (Figure 4 shows an overview). The first 3 stages in this process have already been described: (1) the study HCP will use the prototype DDSS; (2) the patient will consult with a usual HCP; and (3) the patient will consult with the study-provided physician. There are then 2 additional steps: (4) generation of a differential diagnosis by the physician panel, and (5) matching of conditions by the physician panel.

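### The DDSS, usual HCP and study physician are rated on the same patients but compared with independent-sample tests, and the test of DDSS against usual care waits on a three-way test that includes the study physician.

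*Protocol article*

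**What the plan says.** All references are to the protocol article.

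- **Tests.** Under Data Analysis, the question whether the proportions correct for the DDSS, the usual HCPs and the study-provided physicians "are drawn from the same distributions, the chi-squared test will be applied". The next step is conditional. Only if that test is significant, "we will apply a 2-sided post hoc pairwise Fisher exact test to compare the prototype DDSS and the practitioners". The same section names the comparison of the DDSS with usual care as the study goal.
- **Same patients.** Measurement Methods gives the sequence as "1) the study HCP will use the prototype DDSS; (2) the patient will consult with a usual HCP", followed by the study-provided physician. The Stage 1, 2 and 3 sections describe one patient moving through all three. The physician may look at the usual HCP's notes at the end of the Stage 3 consultation. The panel then sets one gold standard list per case, and all the lists are matched to it.
- **Size.** Under Outcomes and Outcome Measures, "The sample size of a minimum of 50 participants was a pragmatic determination", and the pilot is said not to be powered to settle its hypotheses. Data Analysis adds: "Due to the low sample size of this pilot study, it may be the case that the chi-squared tests will not produce significant results".

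No alpha, expected accuracy, within-patient correlation or confidence interval is stated.

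**The concern.** There are two separate problems.

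1. **Pairing is ignored.** A patient with a plain presentation tends to be diagnosed correctly by every source, and a hard case tends to be missed by every source. The three correct/incorrect results are therefore matched within patient. The chi-squared and Fisher tests use only the marginal totals and assume independent groups. Under positive correlation their p-values are too large and power is lost, in a study that has little to spare.

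2. **The gate is in the wrong place.** The first primary endpoint sets DDSS accuracy beside that of the usual HCP. The pairwise test of that contrast is run only after a three-group test has succeeded, and the third group, the study physician, is not part of the contrast. The physician's accuracy can therefore decide whether the main comparison is tested at all.

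**Working it through.** The plan has no derived figure to reproduce, since 50 is described as pragmatic. **Inputs from the protocol article:** n = 50 (a minimum), the three sources, the named tests and the gate. **Assumed here:** alpha 0.05 two-sided, complete data on 50 patients, the accuracies and the within-patient correlation phi.

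**Step 1: direction of the error.** For two ratings on the same n patients, with q = 1 − p,

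Var(difference) = [p1·q1 + p2·q2 − 2·phi·√(p1·q1·p2·q2)] / n.

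At 70% and 50%:
- Pairing ignored: SE = √((0.21 + 0.25)/50) = 0.096.
- phi = 0.3: SE = √((0.46 − 2 × 0.3 × 0.229)/50) = √(0.3225/50) = 0.080.

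The planned tests behave as if phi were 0.

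**Step 2: size of the chi-squared test.** With three equally accurate, equally correlated ratings, the statistic is distributed in large samples as (1 − phi) times a chi-squared on 2 df. The true size is then exp(−5.991 / [2(1 − phi)]).

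| phi | formula | simulated, n = 50, all at 70% |
|---|---|---|
| 0 | 5.0% | 4.9% |
| 0.18 | 2.6% | 2.8% |
| 0.32 | 1.2% | 1.4% |
| 0.48 | 0.3% | 0.4% |

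Cochran's Q at phi 0.32 simulates at 5.0%.

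**Step 3: power for DDSS against usual HCP.** This is a simulation with 50 patients, a shared latent normal factor per patient and accuracies of 70/50/60% (DDSS/usual/physician).

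| phi | Fisher alone | gate plus Fisher (the plan) | exact McNemar |
|---|---|---|---|
| 0 | 46% | 40% | 44% |
| 0.31 | 45% | 37% | 61% |
| 0.45 | 45% | 34% | 71% |

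Repeat runs at phi about 0.3 gave 37–38% and 61–62%. At phi = 0 the two pairwise tests are about equal.

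**Step 4: one data set by hand.** Take 35/50 against 25/50 correct. Fisher gives p = 0.066 however the patients pair up. Exact McNemar is p = 2 × Σ(k ≤ c) C(b+c, k) / 2^(b+c), with b and c the two discordant counts.

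| b, c | both right / both wrong | phi | McNemar p |
|---|---|---|---|
| 14, 4 | 21 / 11 | (21×11 − 14×4)/√(35×15×25×25) = 0.31 | 2 × 4048/262144 = 0.031 |
| 17, 7 | 18 / 8 | (18×8 − 17×7)/572.8 = 0.04 | 2 × 536155/16777216 = 0.064 |
| 20, 10 | 15 / 5 | (15×5 − 20×10)/572.8 = −0.22 | 0.099 |

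The same totals can give different answers, and the planned test cannot tell them apart.

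**Step 5: the gate.** Usual HCP and physician both at 70%, DDSS lower, phi about 0.3, n = 50.

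| gap | gate closes | Cochran's Q would also miss | significant McNemar results blocked by the gate |
|---|---|---|---|
| 10 points | 89% | 77% | 52% |
| 20 points | 45% | 26% | 22% |
| 30 points | 7% | 2% | 3% |

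At a 10-point gap the gate closes 82% of the time even with zero correlation, so small n explains much of it. The physician's rate also matters. At 70/50/60% the gate closes 61% of the time. At 50/70/80%, with the same absolute gap of 20 points between DDSS and usual HCP, it closes 13% of the time.

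**The case against.** The strongest defence is that this is a pilot that disclaims power and says its chi-squared tests may not reach significance. With positive correlation the error costs power and does not create false claims. Descriptive accuracy is reported whether or not the gate opens. All of that stands, and it lowers the severity. It does not make independent-sample tests right for matched data. The general reference to statistics suited to categorical data does not help either, because the specific tests are then named.

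Four stronger readings are tempting, and the documents do not support them:

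- **That the plan's confidence intervals or standard errors are wrong.** Data Analysis specifies none. The claim is limited to test size, p-values and power.
- **That the gate will usually suppress the main comparison.** This depends on the gap, the correlation, the physician's rate and n, and 50 is a minimum. In the equal-comparator case the gate mostly closes up to a gap of about 15 points, is near even at 20 and mostly opens from 25. It withholds only the pairwise test.
- **That the third primary endpoint, the study HCP's "condition suggestion accuracy and comprehensiveness in arm 1 in the preliminary and final DDLs", is given the wrong test.** That comparison is paired, but Data Analysis assigns it no test, and a condensed article may leave that to a fuller document.
- **That the pilot cannot supply inputs for planning the later trial.** Ratings are held per patient, so paired differences and discordant counts can be recovered whichever test is run.

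Conservatism also needs positive correlation. In a run with the DDSS negatively correlated with the other two (phi −0.22), the chi-squared size was 5.9%.

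**Conclusion.** The point holds as a fault in the stated analysis: three ratings of the same patients are compared with tests for independent samples. At n = 50 and phi about 0.3, the chi-squared test works at about 1.2–1.4% instead of 5%. In the 70/50/60% scenario the planned route gives up about 24 percentage points of power against exact McNemar (37–38% against 61–62%). These sizes rest on an assumed alpha, assumed accuracies and an assumed positive correlation. With no correlation, the loss from ignoring pairing disappears.

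The gate is a second fault and does not depend on pairing: the study's own goal should not hang on a test that includes a third group. How often the gate bites ranges from most of the time at small gaps to rarely at large ones.

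This should be fixed but is not critical. The pilot is explicitly unpowered, descriptive accuracy is reported in any case, and the matched data allow a paired analysis.

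**What to change.** In Data Analysis:

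1. Make the patient the unit, and compare the DDSS with the usual HCP by exact McNemar test.
2. Do not make that comparison conditional on the three-way test.
3. Always report the paired difference in top-1, top-3 and top-5 accuracy with its 95% CI and the two discordant counts.
4. If a global comparison of the three sources is wanted, use Cochran's Q in place of the chi-squared test.
5. If the chi-squared/Fisher approach was also meant for the preliminary and final lists in arm 1, use the paired test there too.

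The cost is a change of wording and a few lines of analysis code. No extra data are needed, because every source is already rated patient by patient.
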